## Abstract

**Background:**

The gut microbiome is implicated as a marker of response to  immune checkpoint inhibitors (ICI) based on preclinical mouse models and preliminary observations in limited patient series. Furthermore, early studies suggest faecal microbial transfer may have therapeutic potential, converting ICI non-responders into responders. So far, identification of specific responsible bacterial taxa has been inconsistent, which limits future application. The MITRE study will explore and validate a microbiome signature in a larger scale prospective study across several different cancer types.

**Methods:**

Melanoma, renal cancer and non-small cell lung cancer patients who are planned to receive standard immune checkpoint inhibitors are being recruited to the MITRE study. Longitudinal stool samples are collected prior to treatment, then at 6 weeks, 3, 6 and 12 months during treatment, or at disease progression/recurrence (whichever is sooner), as well as after a severe (≥grade 3 CTCAE v5.0) immune-related adverse event. Additionally, whole blood, plasma, buffy coat, RNA and peripheral blood mononuclear cells (PBMCs) is collected at similar time points and will be used for exploratory analyses. Archival tumour tissue, tumour biopsies at progression/relapse, as well as any biopsies from body organs collected after a severe toxicity are collected. The primary outcome measure is the ability of the microbiome signature to predict 1 year progression-free survival (PFS) in patients with advanced disease. Secondary outcomes include microbiome correlations with toxicity and other efficacy end-points. Biosamples will be used to explore immunological and genomic correlates. A sub-study will evaluate both COVID-19 antigen and antibody associations with the microbiome.

**Discussion:**

There is an urgent need to identify biomarkers that are predictive of treatment response, resistance and toxicity to immunotherapy. The data generated from this study will both help inform patient selection for these drugs and provide information that may allow therapeutic manipulation of the microbiome to improve future patient outcomes.

**Trial registration:**

NCT04107168, ClinicalTrials.gov, registered 09/27/2019.

Protocol V3.2 (16/04/2021).

**Supplementary Information:**

The online version contains supplementary material available at 10.1186/s12885-021-09156-x.

## Background

### The gut microbiome during health and cancer

A healthy individual harbours some 300–500 bacterial species in their gastrointestinal microbiome [1]. While some bacterial genera are common between individuals, the complete composition at strain level taxonomy within any one person is unique, often compared to a “fingerprint”. Our understanding of the human intestinal microbiome, primarily using sequence-based approaches, has developed greatly in recent years. Bacteria make up the majority of the microbial biomass within stool samples and play a central role the development and regulation of our mucosal and systemic immune systems, digestion of food and sustenance, and resistance to pathogens [2]. Pathological imbalances in the microbial community, termed dysbiosis, can be caused by diet, drugs, genetics and infection. Intestinal dysbiosis is linked to a growing list of infectious diseases, autoimmune diseases and syndromes, and could potentially impact the clinical response to therapies, particularly cancer immunotherapy.

The link between human-associated bacteria, cancer development and immunotherapy is not new and pre-dates our recent realization that the human microbiome plays a pervasive role in our health and disease. For example, specific bacterial species are known to cause certain types of cancers, such as gastric cancer caused by *Helicobacter pylori*, while some bacterial agents such as Coley’s Toxin (*Streptococcus pyogenes*) and BCG vaccination have been shown to alter the host response to cancer [3–5]. The mechanisms of action for Coley’s toxin and BCG vaccination remain largely unknown, but these observations highlight an opportunity to use bacteria therapeutically to prevent or treat cancer. Recent evidence suggest that a patient’s intestinal microbiota composition plays a critical, though as yet poorly defined, role in determining both therapeutic efficacy and likelihood of significant adverse events to T-cell checkpoint inhibitor immunotherapy [6–11].

### The gut microbiota as a predictive biomarker for immune checkpoint inhibitor response and toxicity

Immune checkpoint inhibitors (ICIs) are revolutionising treatment of many types of metastatic cancer and signals of efficacy in earlier stages of disease are now emerging. Anti-PD-(L)1 ± anti-CTLA-4 antibodies are now routinely used to treat patients with metastatic cancers, including melanoma [12, 13], renal cancer [14, 15], and non-small cell lung cancer (NSCLC) [16, 17] in expectation of improving overall survival. ICIs are being tested in multiple other cancer types and many new licenses for use are anticipated in the coming years. The first adjuvant ICI trials in patients with resected melanoma at high risk of recurrence have reported improvements in relapse-free survival [18, 19] and adjuvant checkpoint blockade is now being tested in other cancers. While these early indications offer great hope for improving outcomes for cancer patients, ICIs are not without their limitations. Firstly, not all patients respond: response rates vary between 25 and 60% at best, depending on treatment regimen and cancer type; thus most patients embarking on treatment will not benefit [20]. Secondly, immune-related toxicities occur, which are complex, unpredictable, and may be severe or life threatening in up to 50% of treated patients [20]. Thus, significant numbers of patients will be hospitalised to manage toxicity, or require long term (sometimes lifelong) supportive therapies for permanent damage to body systems.

A number of studies using one or two cohorts have associated the gut microbiome with response to ICIs in advanced melanoma, NSCLC and renal cancer [21]. Furthermore, two interventional studies in advanced melanoma have demonstrated that faecal microbiota transplant (FMT) can convert patients that have previously progressed on anti-PD1 immunotherapy to become responsive [22, 23]. Interestingly, ICI-triggered toxicities are also linked to the patients’ microbiome [21] and there is also potential for FMT to ameliorate toxicities [24]. While the mechanisms of efficacy and toxicity remain to be defined, positive clinical outcomes from ICIs may involve stimulation of intestinal dendritic cells and circulating T cells by specific taxonomic groups of intestinal bacteria [8, 25]. Understanding the role of the microbiome may be valuable to guide patient therapy in the future [26] and to develop co-therapies to increase the efficacy of ICIs [21].

Most human microbiome studies performed in cancer patients on immunotherapy have been statistically underpowered and have mainly relied on 16S rRNA gene sequencing, which has taxonomic resolution limited to genus level. Since many beneficial traits in symbiotic bacteria can be distinct to strain level, these approaches most likely provide neither the strain level taxonomic and functional resolution, nor the biological information needed to accurately identify bacterial biomarkers to predict beneficial or detrimental bacterial strains. We have used temporal, deep shotgun metagenomic profiling in a pilot cohort of metastatic melanoma patients treated with ICIs. This was performed using Microbiotica’s platform that comprises the leading Reference Genome Database to give the most comprehensive and precise profiling of the gut microbiome. This gives the resolution necessary to identify bacteria species and even strains linked with outcome. Further, we have been able to show representative strains of the species associated with response have anti-tumour efficacy in vitro and in vivo [27].

We aim to expand knowledge beyond prior studies, both because of the high resolution achieved and because our workflow allows us to culture and archive individual bacterial strains at scale, thus allowing us to test hypotheses using the organisms isolated and identified. Our approach uses large-scale metagenomics of patient cohorts and sample banking, progressing to hypothesis testing using functional studies to fulfil Koch’s postulates for both beneficial and pathogenic bacteria. We will access a variety of in vitro and in vivo pre-clinical models to validate and test beneficial and pathogenic bacteria on host responses, specifically in relation to immunity and tumour growth as well as drug efficacy and toxicity. These functional platforms are critical to develop and progress translational opportunities to enable future patient selection based on microbiome biomarkers to personalise cancer immunotherapy, as well as to precisely manipulate a patient’s microbiota to optimise cancer immunotherapy. Comparison with a limited cohort of healthy household members acting as controls will provide additional essential information about the role of the patient-specific microbiome.

### Impact of COVID-19

COVID-19, also termed severe acute respiratory syndrome coronavirus 2 (SARS-CoV-2), is caused by a coronavirus that is phylogenetically similar to SARS-CoV, the agent of Severe Acute Respiratory Syndrome. Coronaviruses are enveloped positive-sense RNA viruses. In humans, COVID-19 infection is primarily a respiratory disease which can vary from asymptomatic infection through coryzal upper respiratory infection to severe respiratory distress and death. Studies of biomarkers predicting for outcomes from COVID-19 infection have identified several factors associated with immunity including lymphocyte count, neutrophil count, and inflammatory markers such as C-reactive protein, Interleukin-6 and Procalcitonin [28]. In addition, worse outcomes are seen with older age and in males, smokers and diabetics [29]. It is reasonable to assume that COVID-19 may influence (and potentially be influenced by) the microbiome, and therefore we will assess patient COVID-19 status as part of this study.

National arrangements for population and cancer patient COVID-19 testing are evolving and are likely to continue to change during the course of the study. We wish to evaluate both COVID-19 antigen and antibody associations with the microbiome. We will aim to use results available from routine testing where possible, but in the absence of routine testing for either or both of these entities, we will include the option to test within this protocol.

### Rationale for the MITRE study

The pre-treatment presence (and prevalence), or absence of, specific bacterial strains may dictate response and toxicity to immune checkpoint inhibitors.

This hypothesis will be explored and validated in a large-scale prospective study of biological samples collected from patients receiving immune checkpoint inhibitors, as well as household control participants, using our metagenomics platform with matched clinical data.

## Methods/design

### Study design

This is a multi-centre, non-interventional study, involving up to 40 UK sites. Up to 1800 cancer patients and 360 household control participants will be enrolled (Fig. 1).

**Fig. 1 Fig1:**
[figure not shown]
MITRE Study Flow Chart

Cancer patients due to commence standard treatment with systemic therapy including an anti- PD- (L)1 ± anti-CTLA-4 antibody will be invited to take part in this multi-cohort, multi-centre study.

Consenting patients will be asked to provide clinical information and donate biological samples before, during and after completing their treatment (see section Additional file 1), for the duration of the study period, up to a maximum of 5 years.

Consenting patients will also be asked to invite a member of their household to provide limited demographic, health and lifestyle information and biological samples at a single time point only (see Additional file 2).

### Study objectives

#### Primary objective

The primary objective is to assess whether there is a gut microbiome ‘signature’ which can predict for ICI treatment efficacy in patients with advanced, unresectable cancers.

#### Secondary objectives

To determine if the gut microbiome signature predicts for ICI risk of relapse in patients with resected cancers.To evaluate any association with the gut microbiota and ICI-induced toxicity.To assess whether certain medicines (including antibiotics, steroids, proton pump inhibitors (PPIs), non-steroidal analgesics (NSAIDs), probiotics taken within the past 6 months and/or during treatment) affect the gut microbiome signature.To assess whether patients’ diet and body mass index (BMI) affects the gut microbiome signature.To compare and contrast the oral and gut microbiome of patients and their household controls.To study the effects of ICIs on the gut microbiota over time.To establish a unique microbiome biobank of longitudinal samples available for future interrogation.

#### Exploratory objectives

To correlate microbiome findings with patients’ peripheral blood immune and cytokine profiles (including IFNγ, TNFα, IL-6) measured in plasma and PBMCs collected prior to and during treatment.To assess pre-treatment and on-treatment/post-treatment tumour samples for the immunoscore and other immune signatures, including expression of proteins potentially linked to checkpoint inhibitor response, toxicity and immunity.To measure genomic/transcriptomic alterations in blood (including germ-line) and tumours, including (but not limited to) assessment of tumour mutational burden, single nucleotide variants (SNVs) in immune-related genes and HLA status.To measure the presence and nature of any circulating bacterial nucleotides in study patients.To generate primary cell lines from patient PBMCs and tumour tissue to undertake functional immune assays.To explore any interaction between COVID-19 status and the microbiome

### Study outcome measures

#### Primary outcome measure

Based on pilot data and using an iterative process, a putative microbiome signature was defined [27] and will be prospectively evaluated for its ability to stratify cancer patients receiving ICIs into treatment responders and non-responders. The primary outcome measure is the ability to predict for progression-free survival (PFS) of > 1 year. The primary outcome will be determined for an initial series of patient cohorts limited to advanced melanoma, renal cancer and non-small cell lung cancer (NSCLC) (Table 1 and Fig. 2).

**Table 1 Tab1:** Cohorts 1–6 – Advanced disease cohorts and defined standard of care ICI-containing treatment regimens

Cohort	Disease	Regimens	Primary outcome measure
Cohort 1	Unresectable AJCC stage 3 or 4 melanoma	Anti-PD-1 monotherapy (nivolumab or pembrolizumab)	1 year PFS
Cohort 2	Unresectable AJCC stage 3 or 4 melanoma	Ipilimumab+nivolumab	1 year PFS
Cohort 3	Advanced renal cell carcinoma	Anti-PD-(L)1 + kinase inhibitor	1 year PFS
Cohort 4	Advanced renal cell carcinoma	Ipilimumab+nivolumab	1 year PFS
Cohort 5	Advanced NSCLC	Anti-PD-(L)1 monotherapy in the first-line setting	1 year PFS
Cohort 6	Advanced NSCLC	Anti-PD-(L)1 + chemotherapy ± antiangiogenic in the first-line setting	1 year PFS

**Fig. 2 Fig2:**
[figure not shown]
MITRE Patient Cohorts 1–9

#### Secondary outcome measures

The ability of the microbiome signature to predict 6 month PFS, 2 year PFS, overall response rate, median PFS and median overall survival (OS) in cohorts 1–6.The ability of the microbiome signature to predict for 1 and 2 year relapse after resection of high risk melanoma or renal cancer in cohorts 7–9. (Table 2 and Fig. 2)

**Table 2 Tab2:** Cohorts 7–9 – Adjuvant disease cohorts and defined standard of care ICI-containing treatment regimens

Cohort	Disease	Regimen	Primary outcome measure
Cohort 7	Resected AJCC stage 3 or 4 melanoma	Anti-PD-1 monotherapy (nivolumab or pembrolizumab)	1 year & 2 year RFS
Cohort 8	Resected renal cancer	Durvalumab	1 year & 2 year RFS
Cohort 9	Resected renal cancer	Durvalumab+tremelimumab	1 year & 2 year RFS

To compare oral and gut microbiome findings and their association with treatment efficacy.To correlate microbiome findings with incidence and characteristics of CTCAE V5-defined Grade > 3 IrAEs in all enrolled patients, and any association with response to immunosuppressants.To correlate microbiome findings with aspects of pre-existing patient characteristics and behaviour including but not limited to diet, smoking history, BMI, use of antibiotics, steroids, PPIs, NSAIDs and probiotics.To compare the microbiome signature of cancer patients with a household control group of people who are not known to have cancer.To retain a library of biological samples with linked patient data for future research.

#### Exploratory outcome measures

To correlate the gut microbiome findings with the patient’s immune status (HLA subtype, auto-antibodies)To correlate the gut microbiome findings with peripheral immune cell subset composition, surface antigen expression and peripheral blood cytokine (including IFNγ, TNFα, IL-6) and chemokine expressionTo correlate the gut microbiome findings with pre-treatment – and where possible, on-treatment - intratumoural immune cell infiltrate (immunoscore) and microenvironment (including but not limited to CD4, CD8, FOXP3, PD-1, PD-L1, Granzyme B expression)To correlate the gut microbiota findings with tumour mutational burden (measured in tissue and/or circulating free DNA).To undertake next generation sequencing of a defined immune gene panel and assess interactions with the microbiome signature.To measure the presence and nature of any circulating bacterial nucleotides in study patients.To correlate the gut microbiome findings with expression of immune signatures measured using RNAseq, T cell receptor and B cell receptor clonalityTo generate primary cell lines from patient PBMCs and tumour for functional immune assaysTo correlate microbiome findings with COVID-19 status (antigen and/or antibodies detected in nasopharyngeal swab, blood and/or stool)

### Recruitment of patients and eligibility

#### Study population

MITRE is recruiting adult (≥18 years) patients due to commence either adjuvant or palliative treatment with systemic therapy including an anti-PD-(L)1 antibody ± anti-CTLA-4 antibody with a diagnosis of either melanoma, renal cancer, or non-small cell lung cancer. Patients are recruited to 9 cohorts, according to tumour type, treatment and disease stage (Fig. 2).

Patients with advanced disease must have measurable lesions identified within 45 days prior to starting treatment by formal cross-sectional imaging, or clinical measurements. For patients with resected disease, full body imaging must be performed within 12 weeks of planned treatment start date showing no active disease.

Patients with advanced disease must have received no prior ICI for advanced disease. Previous treatment with other types of anti-cancer therapy is allowed, with the exception of NSCLC patients being recruited to cohorts 5 and 6. Prior (neo) adjuvant therapy with ICIs is allowed.

Patients are excluded if they have one or more additional different invasive malignancy diagnosed within the last year not in complete remission, or an additional significant medical or psychiatric condition which would place the patient at undue risk (such as uncontrolled ischaemic heart disease, inflammatory bowel disease, pregnancy/lactation). Regular requirement for non-physiological doses of oral steroids, or regular use of any other immunosuppressive agents is not allowed; regular requirement for prednisolone at a dose of 10 mg or less, or equivalent doses, are allowed. Use of inhaled or topical steroids is also allowed.

All patients must provide written informed consent at registration.

#### Household controls

Cancer patients who consent to take part in the MITRE study will be asked to invite an adult member of their household (age ≥ 18 years) to also take part in this study, to act as a limited control group (up to 360 people will be recruited to this group).

These controls must not have had any gastrointestinal infections in the last 6 months, or have any inflammatory intestinal disease. They must not have taken any antibiotics in the past 6 months, have a history of active cancer, chronic autoimmune disease, significant allergies or an episode of COVID-19 infection requiring hospital admission. Additionally, they should not be taking regular steroids, PPIs, or NSAIDs.

#### Recruitment process

Eligible patients will be invited to participate in this study. Consenting patients will be registered centrally at the Cambridge Clinical Trials Unit – Cancer Theme (CCTU-CT). Patients will be identified in the specialist clinics at the participating centres as per local practice.

### Patient registration

Eligibility criteria must be met before registering the patient on the study. Consenting patients will be registered centrally at the Cambridge Clinical Trials Unit – Cancer Theme (CCTU-CT).

Upon registration, the investigator or designee, must complete the registration electronic CRF (eCRF). Upon completion and submission of these eCRFs the CCTU-CT trial coordinator will check registration eCRFs and assign a unique study ID. This study ID should be used in all future correspondence and patient-related documents.

Any source data transferred should be anonymised to unique study ID, date of birth and patient initials.

### Assessments on study

Patients will be followed up during their routine clinic visits, with study-specific data collection at time points approximating to baseline (pre-treatment), 6–8 weeks, 12 weeks, 3 monthly until 1 year, then 6 monthly thereafter until and including disease progression, or relapse, or study termination.

Immune-related adverse events (IrAEs) will be recorded at each clinic visit.

#### Imaging assessments

Patients will undergo radiological assessment for measurable disease during treatment as per local practice, but is recommended to be done approximately every 12 weeks while on treatment for patients with advanced disease and approximately every 6 months for those patients receiving adjuvant therapy. Imaging frequency after stopping treatment is as per local practice.

The following scans will be reported using RECIST 1.1 criteria for patients with advanced disease:Baseline, pre-treatment scanFor patients on treatment, or off treatment but progression-free: approximately 12 weeks, 6 months, 1 yearAt the time of disease progression, if different to these time-points

Once progression has been confirmed by RECIST 1.1 criteria, further RECIST measurements are not required for the purpose of this study.

### ICI treatment

Specific details of the systemic therapy regimens being used to treat patients taking part in this study are not mandated in this protocol, since this is an observational study. However, all drugs (anti-cancer drugs) as well as any radiotherapy and surgery used to treat cancer during the study period will be recorded in the CRF.

Patients experiencing adverse events while on treatment are managed according to local guidelines. No routine adverse event reporting is being undertaken as part of this protocol.

Documentation of a possible/probable/definite IrAE of CTCAE grade > 3 will trigger the requirement to collect a stool and blood sample within 2 weeks of documentation (Additional file 1).

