### Biological sample collection

A stool sample, oral swab sample, blood samples and routine laboratory data (as per local practice) will be collected at baseline (pre-treatment).

Further stool samples will be collected at approximately 3–6 weeks (ahead of the 6–8 week visit), 9–12 weeks (ahead of the 12 week visit), approx. 6 months, at the time of a CTCAE grade > 3 IrAE, at disease progression, relapse or at 1 year, whichever occurs soonest.

Further blood samples will be taken at a clinic visit approximating to 12 weeks, at 1 year or on progression/relapse, whichever is sooner, and at the time of documenting a significant (CTCAE grade > 3) IrAE.

Patients are asked to consent to allow access to any available archival tumour tissue previously obtained, as well as any excess tumour tissue acquired during the study period (as per local practice).

Patients will also be asked for permission to access any biopsies taken from planned surgery as part of their treatment, including an organ(s) affected by toxicity (e.g. liver or skin biopsy) during the course of this study, to be used for this research.

Registered household controls will be invited to attend a convenient clinic visit with the patient to provide relevant information, have a blood sample taken and receive a stool and oral swab sample collection kit.

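### The abstract sets the severe immune-related event threshold at grade 3 or higher, but the toxicity outcome and the event-sampling triggers say grade above 3, which leaves out grade 3

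*Protocol article*

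**What the plan says.** The protocol article sets a grade threshold for IrAEs in five places.

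- Abstract, Methods: stool is collected at the scheduled times, "as well as after a severe (≥grade 3 CTCAE v5.0) immune-related adverse event".
- Secondary outcome measures: microbiome findings are to be correlated with the "incidence and characteristics of CTCAE V5-defined Grade > 3 IrAEs in all enrolled patients".
- ICI treatment: a possible, probable or definite "IrAE of CTCAE grade > 3 will trigger the requirement to collect a stool and blood sample", within 2 weeks of documentation. Additional file 1 is cited here.
- Biological sample collection, stool: "at the time of a CTCAE grade > 3 IrAE, at disease progression, relapse or at 1 year".
- Biological sample collection, blood: "at the time of documenting a significant (CTCAE grade > 3) IrAE".

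Three other places bear on the point and carry no grade limit. Assessments on study states: "Immune-related adverse events (IrAEs) will be recorded at each clinic visit". The toxicity item under Secondary objectives speaks of ICI-induced toxicity in general. Statistical analysis methods names regularised logistic regression for secondary endpoints such as the incidence of adverse events.

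**The concern.** One threshold in the abstract stands against four in the body, and they cannot both hold. The abstract counts grade 3 as severe; the body's outcome and triggers start at grade 4.

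Two things depend on which rule is used. The first is the event-time sample. A site that works to the body's wording takes no extra stool or blood after a grade 3 IrAE, and no later analysis decision can replace that sample. The second is the definition of a case. Under the body's wording, a patient whose worst IrAE is grade 3 does not meet the toxicity outcome, although the abstract would call that patient's event severe. If the outcome is analysed as yes or no in all enrolled patients, that patient is placed with those who had no severe toxicity. The Discussion gives prediction of severe toxicity a place in its statement of the study's main objective, so the definition matters to what the study can report.

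**Working it through.** The core of the check is a comparison of text. The plan states no figure to reproduce.

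**Step 1: the rules side by side.**

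| Section | Use | Threshold | Grades covered |
|---|---|---|---|
| Abstract, Methods | stool after event | ≥ 3 | 3, 4, 5 |
| Secondary outcome measures | toxicity outcome | > 3 | 4, 5 |
| ICI treatment | stool and blood trigger | > 3 | 4, 5 |
| Biological sample collection | stool schedule | > 3 | 4, 5 |
| Biological sample collection | blood schedule | > 3 | 4, 5 |

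CTCAE grades are whole numbers, so the rules differ by grade 3 and nothing else. No section of the body uses grade 3 or higher for IrAEs.

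**Step 2: what survives under the body's wording.** IrAEs are recorded at each clinic visit without a grade limit. Baseline and scheduled stool and blood are collected whatever the toxicity. What is lost is the event-triggered sample and the patient's place in the grade-defined outcome. Only the first of these is beyond repair.

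**Step 3: size, as an illustration.** The article does not split grade 3 from grades 4–5, so the loss cannot be computed from it. Inputs:

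- *s*, the share of grade 3 or higher toxicity that is grade 3: 0.70 to 0.90 (assumption, applied both to events and to patients by worst grade).
- *p*, the proportion of patients with grade 3 or higher toxicity: 0.20 (assumption) and 0.50. The latter is the upper limit that the Background gives for severe or life-threatening toxicity. The Background does not tie that phrase to a CTCAE grade, so equating the two is also an assumption.

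Share of event samples and of grade-defined cases lost = *s* = 70% to 90%, whatever *p* is.

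If the outcome is binary in all enrolled patients, the share of non-cases who are grade 3 patients = *ps* / (1 − *p*(1 − *s*)):

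| *p* | *s* | Grade 3 patients | Non-cases | Share |
|---|---|---|---|---|
| 0.20 | 0.70 | 0.14 | 1 − 0.06 = 0.94 | 15% |
| 0.20 | 0.90 | 0.18 | 1 − 0.02 = 0.98 | 18% |
| 0.50 | 0.70 | 0.35 | 1 − 0.15 = 0.85 | 41% |
| 0.50 | 0.90 | 0.45 | 1 − 0.05 = 0.95 | 47% |

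The proportional loss of cases does not depend on the overall rate. The mixing of the comparison group depends on it strongly.

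**The case against.** **A notation slip.** The body's sign may be a lost or mistyped ≥, and the abstract's severe event and the body's significant event look like the same trigger. That is possible. However, ≥ appears correctly in the abstract and in the eligibility text, while the strict sign appears four times in three sections. If it is a slip, it sits in the operative instructions and still needs correcting.

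**Sites may not work from the article.** They work from the full protocol and Additional file 1, neither of which is shown, and either may carry the intended threshold. This stands: actual sample loss is not established. The contradiction within the article remains whatever those documents say.

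**The data are not lost.** IrAEs of every grade are recorded, and the study's hypothesis concerns pre-treatment bacteria, for which the baseline sample is taken regardless. This also stands. It confines the irrecoverable part to the extra event-time samples and leaves the outcome definition open to correction at analysis.

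**Stronger readings.** A reader might infer that the analysis will count grade 3 patients as non-cases. The article does not say so: the outcome is worded as a correlation, the analysis section gives no grade limit for adverse events, and detail is left to a statistical analysis plan. That dilution follows only if the outcome is analysed as a binary, and a weaker association follows only if grade 3 and grade 4–5 events share the same link with the microbiome.

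A reader might also infer that toxicity cases shrink to a handful by taking the first-stage cohort size: 50 × 0.50 = 25, falling to 50 × 0.05 = 2.5 or 50 × 0.15 = 7.5. That denominator is wrong. The outcome covers all enrolled patients, up to 1800, where the same rates give 1800 × 0.05 = 90 to 1800 × 0.15 = 270. Those rates themselves hold the Background's upper limit of 50% as if it were the expected value.

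**Conclusion.** The contradiction is certain from the text: grade 3 or higher in the abstract, above grade 3 in the toxicity outcome and in every sampling trigger in the body. The consequences are conditional. If sites follow the body as written, grade 3 IrAEs yield no event stool or blood and fall outside the grade-defined outcome. Under an assumed grade 3 share of 70–90%, the same percentage of event samples and grade-defined cases would go. The share of grade 3 patients among non-cases would be about 15–18% at an assumed 20% severe rate, rising to 41–47% only at the 50% ceiling, and only in a binary analysis.

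This should be fixed, but it does not threaten the study's main result. It touches one secondary outcome and an additional sample, and 1-year PFS is untouched. The reason to act during recruitment is that event samples not taken cannot be replaced, whereas the outcome definition can be corrected later from the recorded IrAEs.

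**What to change.** Use one research threshold for the toxicity outcome and for the event-sampling trigger in the Abstract, Secondary outcome measures, ICI treatment and Biological sample collection. Grade 3 or higher (CTCAE v5.0) is the threshold that matches the abstract's own definition of severe. Check the wording against Additional file 1, and notify sites while sampling is ongoing.

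The cost is a wording correction, a site notice and more event sample kits if sites have been working to the stricter limit. The change concerns only the research outcome and the sample trigger; patient care is unaffected.
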